## Methods and analysis

### Study design and setting

This is an unmatched case-control study involving 240 couples with impaired male fertility (cases) and 240 couples with normal male fertility (controls). Participants are planned to be recruited between July 2024 and June 2026 from KK Women’s and Children’s Hospital (KKH), Singapore. The current protocol is version 1, dated 26 March 2024.

### Participants and recruitment

Couples from the case group will be recruited from the infertility clinics in KKH, while couples from the control group will be recruited from the antenatal clinics in KKH. The team will recruit potential participants through local advertising in the hospital. We will collaborate with obstetricians and gynaecologists at KKH to obtain participant referrals. Moreover, active screening of potential participants will be conducted in the clinics. Other than from the antenatal and infertility clinics, the team will also leverage the Healthy Early Life Moments in Singapore (HELMS) programme to recruit potential cases and controls. HELMS is a new programme established at KKH in April 2022 to provide a continuum care for women with obesity in the general population before, during, and after pregnancy.^43^

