#### Cases

Men aged 21–49 years.Men with a female partner aged 21–39 years.Couples who are not able to conceive for at least 12 months of regular, unprotected intercourse.Couples who are Singapore citizens or permanent residents.

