#### Controls

Men aged 21–49 years.Men with a female partner aged 21–39 years.Men with proven fertility indicated by female partners who are currently pregnant and with viable intrauterine pregnancy at gestational weeks of less than or equal to 16 at the time of the study.Couples with attempted time to conceive within 12 months to achieve this pregnancy.Couples who are Singapore citizens or permanent residents.

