#### Cases

Male infertility of a known aetiology, including azoospermia, retrograde ejaculation, genetic disorders, cancer treatment, or testicular trauma.Female infertility diagnosis as confirmed by diagnostic imaging or having severe endometriosis.Female partners with an irregular menstrual cycle of >35 days.Couples with known chromosomal abnormalities.

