### Data collection and management

During the study visit (the only single timepoint visit), trained research staff will collect data on the sociodemographics and medical history of participants through interviews and medical record collection forms. They will also gather self-reported data on behavioural, lifestyle and environmental factor exposures from the past month using standardised questionnaires. The selection of the recall timeframe is based on the period specified in the validated questionnaires (table 1). Additionally, the staff will conduct anthropometric and body fat composition measurements, and collect blood, urine and semen samples from participants at the clinics in KKH. All data will be saved in a REDCap database. Access to this database is secured with a password, and only approved study team members can access the stored information.

**Table 1 T1:** Data and biosamples collected from both case and control participants

Male partners	Parameters
Sociodemographic, clinical, behavioural, lifestyle and environmental factors	Age, country of origin, length of time in Singapore if born overseas, ethnicity, education, occupation, monthly income, medical history, medication, family history, reproductive health history, male sexual function,^60^ environmental exposure, cigarette smoking, sleep,^61^ stress,^62^ dietary supplement intake, dietary and alcohol intake,^63^ chrononutrition profile,^64^ physical activity,^65^ sedentary behaviour
Anthropometric and blood pressure measures	Body height, weight, body fat composition (InBody 970, USA), blood pressure
Biochemical tests (blood/urine samples)	HbA1c, lipid profile, cortisol, oxidative stress, inflammatory biomarkers, environmental pollutants (endocrine-disrupting chemicals), exosomes, microbial-derived metabolites
Semen analysis	Semen volume, sperm density, sperm motility, sperm morphology, sperm DNA fragmentation
Molecular analysis	mRNA expressions, sncRNA expression, DNA methylation

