Given that the fertility index comprises male and female factors, we will perform additional analyses to evaluate the individual performance of the index that includes only male factors or female factors using the AUROC. We will also evaluate the performance of the male factor index, with adjustment of female factor index.

#### Aim 3

We will use multivariable linear regression to examine the association between modifiable factors and semen parameters, adjusting for sociodemographic factors.

To understand the relationships between male factors and fertility indices across different conception methods, we will replicate the above analyses by examining outcomes based on assisted and unassisted conception. To assess potential selection bias in both studies, we will compare baseline characteristics between participants with and without a complete set of data. We will use multiple imputation by chained equation to handle missing values.^54^ Sensitivity analyses will be conducted using only samples with complete data. To further ensure robustness, we will test interactions between male and female factors and stratify analyses by key confounders. Statistical analyses will be conducted using the Stata Statistical Software.

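### Male supplement use is recorded only after conception has failed, so use begun because of that failure can pass for a marker of infertility (Aims 1 and 2) or a correlate of poor semen (Aim 3)

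*Protocol article*

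**What the plan says.** All references are to the protocol article.

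- **Who the cases are.** Under Participants and recruitment, "Couples from the case group will be recruited from the infertility clinics in KKH"; controls come from the antenatal clinics, and the HELMS programme may supply both groups. The inclusion criterion for cases is "Couples who are not able to conceive for at least 12 months of regular, unprotected intercourse".
- **Who the controls are.** Their partners are currently pregnant, with the further criterion "Couples with attempted time to conceive within 12 months to achieve this pregnancy". The exclusions for controls rule out donor gametes but not other assisted conception.
- **When exposure is measured.** Data collection and management describes a single visit, at which staff gather "self-reported data on behavioural, lifestyle and environmental factor exposures from the past month using standardised questionnaires". Table 1 lists male dietary supplement intake in the row that holds the behavioural and lifestyle items. The last paragraph of the Introduction before Figure 1 counts behavioural and lifestyle factors as modifiable exposures.
- **How it is analysed.** Aim 1 selects male factors by LASSO in a logistic model of case status. Aim 2 carries the selected factors into a points index in which more points mean a better chance of pregnancy. Aim 3 will "examine the association between modifiable factors and semen parameters, adjusting for sociodemographic factors".
- **What is excluded.** The exclusion for case men is "Male infertility of a known aetiology, including azoospermia, retrograde ejaculation, genetic disorders, cancer treatment, or testicular trauma". Neither group has an exclusion or separate handling for products taken because of difficulty conceiving.

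**The concern.** For every case, the past-month window falls after the outcome has occurred. A man who starts a supplement because the couple has not conceived is exposed as a result of being a case. In a model of case status that supplement looks like a risk marker even if it does nothing. If it helps, the benefit is diluted or its sign reversed.

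Three results are at stake:

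- **Aim 1** could select supplement use as a male factor associated with failure to conceive.
- **Aim 2** could give it unfavourable points in an index meant for community use.
- **Aim 3** could associate it with worse semen, because users would be disproportionately cases and sociodemographic adjustment does not address that.

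The safeguards described (directed acyclic graphs to choose confounders, propensity scores, interaction tests, stratification) deal with common causes of exposure and outcome. They do not repair an exposure that the outcome produced, unless the data separate such use from other use. The limitations paragraph names recall bias and residual confounding but not this mechanism.

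**Working it through.** **Plan's own figure.** The article gives no rate of supplement use and no expected association for it, so there is no figure to reproduce. The only plan inputs used are 240 men per group and a two-sided 5% level (Sample size). Everything else is assumed.

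**Assumptions.** Background use b is the same in both groups. A share s of case non-users and a share t of control non-users start because of difficulty conceiving. Unless stated, the product has no effect.

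**Step 1: odds ratio for being a case (Aims 1 and 2).**
Use in cases: pc = b + (1 − b)s. Use in controls: p0 = b + (1 − b)t. OR = [pc/(1 − pc)] / [p0/(1 − p0)].

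With b = 0.20 and s = 0.20, pc = 0.20 + 0.80 × 0.20 = 0.36.

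- t = 0: p0 = 0.20; OR = (0.36/0.64)/(0.20/0.80) = 0.5625/0.25 = 2.25.
- t = 0.10: p0 = 0.20 + 0.80 × 0.10 = 0.28; OR = 0.5625/(0.28/0.72) = 0.5625/0.3889 = 1.45.
- t = 0.20: p0 = 0.36; OR = 1.00.

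Range with no control uptake (t = 0):

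| Background use b | s = 5% | s = 10% | s = 20% | s = 30% |
|---|---|---|---|---|
| 10% | 1.53 | 2.11 | 3.50 | 5.29 |
| 20% | 1.26 | 1.56 | 2.25 | 3.14 |
| 30% | 1.18 | 1.37 | 1.83 | 2.43 |

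These are upper values for each b and s, because any control uptake lowers them.

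**Step 2: chance of a false finding in a simple two-group comparison.**
Power = Φ{[d − 1.96·√(2p̄(1 − p̄)/240)] / √([pc(1 − pc) + p0(1 − p0)]/240)}, where d = pc − p0 and p̄ is their mean.

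- 0.36 v 0.20: (0.16 − 1.96 × 0.0410)/0.0403 = 1.98, so 98%.
- 0.36 v 0.28: (0.08 − 1.96 × 0.0426)/0.0424 = −0.08, so 47%.

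**Step 3: a product that helps (true OR 0.70, b = 0.20, s = 0.20).**
Odds of use in cases before any starting: 0.70 × 0.25 = 0.175, a proportion of 0.149. After starting: 0.149 + 0.851 × 0.20 = 0.319, odds 0.469.

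- t = 0: OR = 0.469/0.25 = 1.88.
- t = 0.10: OR = 0.469/0.3889 = 1.21.

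The sign reverses in both. With s = 5% and t = 0, the OR is 0.95 at b = 20% and 0.86 at b = 30%: weakened, not reversed.

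**Step 4: Aim 3, cases and controls pooled 1:1.**
Suppose semen in cases is worse by D standard deviations, and use is unrelated to semen within each group. The apparent effect of a null product is −D × [P(case | user) − P(case | non-user)].

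- 0.36 v 0.20: P(case | user) = 0.36/0.56 = 0.643; P(case | non-user) = 0.64/1.44 = 0.444; difference 0.198. For D = 0.3, 0.5 and 0.8 the shift is −0.06, −0.10 and −0.16 SD.
- 0.36 v 0.28: 0.36/0.64 = 0.563; 0.64/1.36 = 0.471; difference 0.092. The shift is −0.03, −0.05 and −0.07 SD.

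This step does not require that men start because of a poor semen result. It requires only that cases have worse semen on average and use more.

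**The case against.** The strongest reply has five parts.

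1. **Controls can have the same motive.** They may have tried for up to 12 months, may have conceived with assistance (the plan repeats its analyses by assisted and unassisted conception), and may come through HELMS. A reader might infer that fertility-motivated use can arise only among cases; the eligibility criteria do not support that. This stands, and it is why the illustration falls from 2.25 to 1.45 with modest control uptake and vanishes with equal uptake.
2. **Medication is a different matter.** A reader might infer that male medication also enters as a modifiable factor over the past month. The article does not say so. Table 1 lists it beside medical history, the past-month window is tied to behavioural, lifestyle and environmental exposures, and medication could be adjusted for as general health in Aim 1. The point therefore rests on supplements. Even there the article does not list the candidate variables, though Table 1 and the definition of modifiable exposures point that way.
3. **Knowledge of semen results.** A reader might infer that men who start supplements already know their semen is poor. No passage says so, and case status has no semen criterion.
4. **Detail in the forms, and acknowledged limits.** The forms may capture start and reason, which an article need not report. Aim 3 is exploratory, and the Discussion calls causal links inferential. That moderates the weight of the point. It does not change the stated recall window or the stated Aim 3 adjustment.
5. **Recall.** Counting only use begun before the couple started trying would ask cases to recall at least 12 months back and many controls less, against the plan's aim of avoiding long recall. This stands and limits the remedy.

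**Conclusion.** The point holds for male dietary supplement intake, as a risk that the design creates rather than a demonstrated bias. It rests on three stated features: a past-month window at a single visit, at least 12 months of failed conception before that visit in every case, and sociodemographic adjustment only in Aim 3. It also assumes that supplement intake is among the candidate male factors and that fertility-motivated use is more common in cases than in controls. The second is likely, since all cases have the motive and only some controls do.

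The size cannot be settled from the documents. In the 20%/20% illustration the spurious odds ratio is 2.25 without control uptake and 1.45 with 10% uptake; with few starters or similar uptake in both groups it is small or absent. The Aim 3 shift in that illustration is 0.03 to 0.16 SD. The change is worth making now, because reason and start of use have to be asked at the only visit.

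**What to change.** **At the visit, in both groups:** for each male supplement, and for any fertility-directed medication, record the reason (for fertility: yes/no) and the approximate start.

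**Aims 1 and 2:** keep fertility-motivated use out of the LASSO candidates and the index points. Use for other reasons can remain a candidate.

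**Aim 3:** adjust for fertility-motivated use, and repeat the semen and oxidative analyses without the men who report it.

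**Sensitivity analysis only:** restrict to use begun before the couple started trying. It should not be the main rule, because recall would be long and unequal between groups.

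**Cost:** two extra form items and a few sentences of analysis plan. The stated reason will carry some recall error, and the repeat analysis will have a smaller sample. If the existing forms already hold both items, only the analysis wording needs to change.

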We will include the identified male factors from aim 1, along with female factors which are known to be associated with successful pregnancy in a multivariable logistic regression. The male factors will focus on those easily accessible measurements. The female factors include age, BMI, smoking exposure, dietary habit, alcohol consumption and folic acid supplementation, which we have identified in our previous study.^52^ We will also include some important clinical data and other maternal factors such as the duration of active conception attempts, sexual health issues and probable depression in the logistic regression to further select the predictors. To ensure accuracy, we will use weighted logistic regression, adjusting the model based on the updated prevalence of successful pregnancies within a year in the population to correct for sampling biases. The best-fitting model will be determined using Akaike’s information criteria. Subsequently, we will create a point-based scoring system based on the final model coefficients,^53^ making it easily applicable in community settings. Integer points will be assigned depending on the presence or absence of each factor, allowing the estimation of overall probability by summing the points. Higher point values will indicate higher chances of pregnancy. To facilitate calculation of the fertility index score, all continuous variables will be categorised based on clinical thresholds or appropriate percentiles prior to the analysis. We will repeat the same procedures by including male metabolic biomarkers and semen parameters that are associated with successful pregnancy in the weighted logistic regression. This will enable the generation of various versions of the fertility index, catering to different levels of complexity for application in primary and tertiary care settings.

Subsequently, we will use 10-fold cross-validation to assess the performance of the derived logistic regression models and respective fertility index scores. This cross-validation procedure helps evaluate the model’s performance on different subsets of the data, providing an estimate of its predictive ability and generalisation performance. The fertility index will be evaluated for its discriminatory ability in predicting chances of pregnancy based on the area under the receiver operating characteristic curve (AUROC), with value >0.80 indicating that the model exhibits a good discriminatory ability or predictive value.

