### Sample size

There is no straightforward, universally accepted method to estimate the required number of participants for developing a multivariable prediction model. Thus, we employed a few alternative methods to estimate the sample size required. We used paternal BMI as an indicator reflective of paternal lifestyle and metabolic factors that are associated with successful pregnancy and expect that it may be retained in the prediction model. Based on the assumption that males with impaired fertility will have an average BMI 1.3 unit higher than the fertile males,^55 56^ and considering a BMI SD of 4 kg/m^2^, a two-sided 5% type 1 error rate and a power of 90%, the minimum required sample size to detect a difference in BMI between cases and controls is 400 couples (200 cases:200 controls). Considering a variance inflation factor of 1.2 for adjustment of maternal factors and other covariates, the study will need to recruit 480 couples (240 cases:240 controls).

Previous studies have reported the use of the event per variable (EPV) ratio:the number of events (success pregnancy) divided by the number of regression coefficients in the model to determine the sample size of a multivariable model.^57^ An EPV of at least 10 has been recommended to avoid overfitting.^58^ We estimate 15 regression coefficients based on the independent male predicting factors of successful pregnancy in the logistic model. Following this guideline, we require 150 events. Given the observed pregnancy rate of 48% in the population,^59^ the total sample size calculated to achieve this number of events is approximately 313 (150/0.48). By accounting for a variance inflation rate of 1.2 for correlation between male and female factors, we will require 376 couples (188 cases:188 controls) in the study.

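### Recruiting some couples through a programme for women with obesity lets the recruitment mix shape the female BMI coefficient in the Aim 2 index, and no stated weighting or adjustment corrects it

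*Protocol article*

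**What the plan says.** Under Participants and recruitment, the protocol article names two main sources. For cases, "Couples from the case group will be recruited from the infertility clinics in KKH"; controls come from the antenatal clinics of the same hospital. It then adds a third source for both groups: "the team will also leverage the Healthy Early Life Moments in Singapore (HELMS) programme to recruit potential cases and controls". HELMS is described as a programme "to provide a continuum care for women with obesity in the general population before, during, and after pregnancy". The design is unmatched, with 240 cases and 240 controls, and the article states no quota, cap or balance by source.

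In the Statistical analysis plan, Aim 2 builds a logistic model and turns its coefficients into points. Among its predictors, "The female factors include age, BMI, smoking exposure, dietary habit, alcohol consumption and folic acid supplementation". Continuous variables are to be categorised at clinical thresholds or at percentiles. The model is weighted by the population prevalence of pregnancy within a year, with the stated purpose of correcting sampling bias.

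Aim 1 adjusts for female factors related to both the male factors and pregnancy, and will explore inverse probability weighting to balance confounders. Stratification by key confounders is also planned. None of these steps names recruitment source, and the limitations in the Discussion do not mention it.

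Under Sample size, the study is sized on paternal BMI: "We used paternal BMI as an indicator reflective of paternal lifestyle and metabolic factors that are associated with successful pregnancy".

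**The concern.** HELMS couples enter the study because the woman has obesity, and female BMI is one of the exposures that Aim 2 estimates and converts to points. This is sampling on an exposure. The proportion of obese women among cases and among controls then reflects two things: the real association with fertility, and how many HELMS couples were enrolled into each group. A pooled model without a source term cannot separate them.

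At stake are the female BMI points in the index and the probabilities derived from the total score. The index is meant for community use, so a coefficient that partly records where couples were found would carry over wrongly. Percentile cut-points have a related problem: a sample enriched for female obesity has higher BMI percentiles than the population in which the score will be applied, even when both groups are enriched equally.

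**Working it through.** **1. The plan's own figure.** Inputs from Sample size: difference 1.3, SD 4, two-sided 5%, power 90%. Per group, n = 2 × (1.960 + 1.282)² × 4² / 1.3² ≈ 199, so 398 in total. The article states 400, and 400 × 1.2 = 480. The figure reproduces, and the sample-size arithmetic is not in question.

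**2. What source-dependent sampling does to the coefficients.** Let s(F, Y) be the chance that a couple with female BMI F and status Y (1 = case, 0 = control) is enrolled. If enrolment depends only on F and Y, then for male factors M:

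logit P(case | M, F, enrolled) = logit P(case | M, F) + log[ s(F,1) / s(F,0) ]

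The extra term depends on F alone. Adjusting adequately for F leaves the coefficients of M intact, but the extra term goes into the coefficient of F.

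**3. What the prevalence weight does.** It multiplies all cases by one constant, w1, and all controls by another, w0. For a 2×2 table with a obese and b non-obese cases, and c obese and d non-obese controls, the weighted odds ratio is (w1·a × w0·d) / (w1·b × w0·c) = ad/bc. The weight resets the case:control ratio and leaves the excess of obese women as it was.

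**4. Size for female obesity.** Assumptions, none given in the documents: every HELMS woman is obese, and 10% of other women are. With HELMS share h, the obese proportion is h + (1 − h) × 0.10 if there is no true effect. Odds ratios are crude and are for being a case.

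| HELMS share, cases / controls | Obese, cases / controls | Odds ratio (truth = 1) |
|---|---|---|
| 10% / 10% | 0.19 / 0.19 | 1.00 |
| 20% / 10% | 0.28 / 0.19 | (0.28/0.72) / (0.19/0.81) ≈ 1.66 |
| 30% / 10% | 0.37 / 0.19 | (0.37/0.63) / (0.19/0.81) ≈ 2.5 |
| 10% / 30% | 0.19 / 0.37 | ≈ 0.40 |

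**5. Equal shares with a true effect.** Take a true odds ratio of 2 among clinic couples: 10% of controls are obese (odds 0.111), so cases have odds 0.222, or 18.2%. Add 20% HELMS to each group.
- Cases: 0.20 + 0.80 × 0.182 = 0.345
- Controls: 0.20 + 0.80 × 0.10 = 0.28
- Odds ratio: (0.345/0.655) / (0.28/0.72) ≈ 1.36

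Equal shares avoid a false association but shrink a real one. In these examples a HELMS term restores the true value, because the obesity contrast is then estimated within clinic couples.

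**6. Cut-points.** In the 20% / 10% case with equal group sizes, the pooled obese proportion is (0.28 + 0.19)/2 = 0.235. The obesity threshold is the 90th percentile among clinic couples but about the 76th in the pooled sample.

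**7. Paternal BMI.** Assume HELMS women are 8 kg/m² heavier, SDs are 4.5 (women, assumed) and 4 (men, from the article), and the couple correlation r is 0.2 to 0.4. The crude spurious male difference is (share difference) × 8 × r × 4/4.5.
- 20% v 5%: 1.2 × r × 0.889 = 0.2 to 0.4, or 16% to 33% of 1.3
- 30% v 10%: 1.6 × r × 0.889 = 0.3 to 0.6, or 22% to 44% of 1.3

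In this model the male difference arises only through female BMI. By step 2, adjustment for female BMI removes it, so these figures describe an unadjusted contrast, whereas the Aim 1 analysis is adjusted.

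**The case against.** The strongest reply has four parts.

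- **Safeguards are planned.** Aim 1 adjusts for female factors and will explore weighting, and stratification follows. This stands for the male coefficients. A reader might infer that HELMS recruitment also biases the paternal BMI contrast on which the study is sized. The documents do not support that: the route runs through similarity between partners, which the article does not quantify, and through female BMI, which meets the article's criterion for adjustment. The safeguards do not rescue the female BMI coefficient in Aim 2.
- **The shares may turn out equal, and the full protocol may set quotas.** No passage says that shares will differ, and an article may leave such detail out. This limits the point to a risk. But equal shares still attenuate a true effect (working, step 5), and the article does state a remedy for sampling bias, the prevalence weight, that does not reach this problem.
- **HELMS care might change past-month habits.** A reader might infer this too. The article does not say that HELMS changes either partner's diet or activity, so it forms no part of the finding.
- **Restricting the primary analysis to clinic couples would be costly.** This stands. HELMS is the one named programme that supplies both groups. At shares of 30% and 10%, with no replacement recruitment, 168 cases and 216 controls remain. With the 1.2 inflation, the standard error is 4 × √(1.2 × (1/168 + 1/216)) ≈ 0.45, and power for 1.3 units falls from about 90% to about 82%. At 20% and 5% it is about 86%.

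**Conclusion.** The concern holds for female BMI in the Aim 2 index. As the article describes it, the coefficient and any percentile cut-points can depend on the HELMS share in each group, and neither the prevalence weight nor adjustment for female BMI corrects that. In the illustrations, a null odds ratio moves to between about 0.40 and 2.5 when shares differ by up to 20 percentage points, and a true odds ratio of 2 falls to about 1.36 at equal shares of 20%. These sizes rest on assumed HELMS shares and obesity rates and on crude odds ratios; the actual distortion could be negligible if few HELMS couples enrol.

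It does not extend to the male coefficients in general. If HELMS enrolment depends only on female BMI and case status, the planned adjustment protects most of them, subject to how well female BMI is modelled.

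**What to change.** - Record recruitment source (infertility clinic, antenatal clinic, HELMS) for every couple, and report the HELMS share by group.
- Include HELMS (yes/no) as a term or stratum in the Aim 1 and Aim 2 models. The two clinics cannot be separate terms, because each supplies only one group. The HELMS term is a design variable and should carry no index points.
- Set BMI cut-points from clinical thresholds, which the plan already allows, and not from pooled percentiles.
- Repeat Aims 1 and 2 without HELMS couples as a sensitivity analysis. A clinic-only primary set is not needed.

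The cost is one data field, one model term and slightly less precision for the female BMI coefficient. Source is easiest to capture while recruitment is open, which the article plans until June 2026.
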